**9. Observation of Adverse Event**

9.1 Definition

(1) Adverse event (AE): any unfavorable medical incident happens since the time when the subject signs the informed consent and enrolls the trial to the finish of the last follow-up is judged as adverse event, no matter whether the medical incident is associated with the investigational drug or not.

(2) Significant adverse event: besides severe adverse event, any adverse event happens and causes the use of pointed medical measures (e.g. drug withdrawal, reducing dosage and expectant treatment) and hematological and/or other laboratorial anomaly.

9.2 Criteria for Judging Intensity of Adverse Event

All clinical adverse events occurred in this clinical research will be recorded on the adverse events page of CRF and classified according to the intensity. In order to have a unified standard, the intensity grade of events is as follows:

Slight perceptible malaise but not affect daily activities

Moderate stronger malaise leading to affect or reduce daily activities

Severe malaise that unable to work or carry out daily activities

It needs to pay attention to distinguish the severity and intensity of adverse events. Severity is used to describe intensity and it may not be a serious adverse event (SAE).

9.3 Judging standard of the relation between adverse events and investigational drug

The causality analysis of the relation between all adverse events and the investigational drug is judged according to five grades, i.e. certainly related, probably related, possibly related, possibly unrelated and definitely unrelated. The first three grades are judged drug adverse reaction. In the causality analysis we consider the following five aspects.

1) Do the time of beginning to use the medicine and the time of appearance of Adverse Drug Reaction (ADR) have reasonable precedence relation (appearance during using medicine)?

2) Does the suspected ADR match the already-known ADR of the drug (conformity with the literature)?

3) Can the suspected ADR be explained by influences of combining with drug, original drug, clinical state of patients or the effect of other therapies (other explanations)?

4) Do the suspicious ADR disappear or reduce after drug withdrawal or decrement (withdrawal symptom)?

5) Does suspicious ADR appear again after taking the same medicine (taking again, appearing again)?

9.4 Abnormal laboratory results

The investigator should judge whether the abnormal laboratory results are of clinical significance and provide possible interpretation. The reported adverse event which causes the abnormal laboratory results should also be recorded as adverse events in ADR.

- 9.5 Follow-up and adverse event record

Adverse events, especially the events which have a connection with the investigational drugs, should be followed up until they return to the baseline or tend to be steady. If follow-up can’t make the adverse events back to the baseline or to be steady, then it should be recorded and explained in the CRF. Any serious adverse events occurred in the clinical trial must be reported to the sponsor and major research institution within 24 hours. At the same time, the investigator must fill in the SAR report and record the  occurrence time, seriousness, duration, measurement and turnover.

**10. Data management**

Researchers should load original observation record of subject into case report table  correctly, completely, clearly and timely. Supervisor should confirm that the trail is carried out according to trail scheme, and all case report tables are filled correctly and completely, the data is consistent with original materials. If there is any mistake or omission, researcher should correct it immediately. After being checked, the case report table should be submitted to data administrator of clinical trial by supervisor.

If there is any problem, data administrator should inform supervisor immediately,  and ask researcher to make an explanation. Query table should be used to record various questions and answers, and kept properly for reference.

**11. Statistical Analysis**

11.1 Analysis set

Full analysis set (FAS): it refers to the data set of all subjects participating in

randomization and being evaluated after medication at least once. For those subjects who fail to observe all healing effect evaluation, we conduct the data transfer according to LOCF (last observation carry forward) principle.

Per protocol set (PPS): it refers to the data set of all subjects meeting inclusion criteria, inconsistent with exclusion criteria and completing therapeutic scheme. Analysis (per protocol, PP) is taken on data of all cases consistent with research scheme, with good dependency and completion of filling in contents specified by CRF.

Safety set (SS): It refers to the data set of subjects who are grouped at random, take the research drug and at least have one safety assessment after the baseline.

Baseline comparative analysis and curative effect analysis are conducted based on

FAS and PPS, and safety evaluation is conducted according to SS.

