**6. Trial discontinuation or modification**

The participants will be able to end participation or withdraw consent at their own request at any time. Participants will be withdrawn from the trial if they suffer from an unexpected serious adverse event.

Under some circumstances, certain modifications to the manufacturing changes, and/or to the clinical protocol during the course of the clinical investigation can be made. Any such changes will be required to report to IRB for approval.

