6.2 Subject withdraw research voluntarily

According to informed consent, subject has the right to withdraw research; if the subject does not put forward the idea of withdrawing research clearly, but losses to follow up for refusal taking medication or detection, he or she also withdraws researcher (or “off”). The reason of withdraw should be comprehended and recorded.

The history record table should be preserved for the subject who withdraws research for any reasons, the last detection result can be considered as final result, and curative efficacy and adverse effect should take full data set analysis.

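### Carrying the last result forward records on-treatment cures as cures at week 4, which hides relapse and can favour a non-inferiority finding

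*Protocol*

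**What the plan says.** Protocol section 11.1 defines the full analysis set (FAS) as randomised subjects "being evaluated after medication at least once". For subjects who lack some efficacy evaluations it then states: "we conduct the data transfer according to LOCF (last observation carry forward) principle". No visit is excepted.

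Section 6.2 says of subjects who withdraw that "the last detection result can be considered as final result, and curative efficacy and adverse effect should take full data set analysis". It also treats as withdrawn a subject who "losses to follow up for refusal taking medication or detection". Section 6 adds: "Participants will be withdrawn from the trial if they suffer from an unexpected serious adverse event".

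The outcome these rules feed is set elsewhere:
- Section 5.1 makes clinical cure, short and long term, the primary outcome.
- Section 5.2 lists re-infection among the failures, but ties the definition of cure to Day 7 or Day 14 and names no follow-up day.
- Section 8.3 repeats the clinical and laboratory examination at visit 4, two weeks after treatment ends (week 4 in section 5.2).

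Section 11.2 calls the approach non-inferiority. Section 3.2 allows for 20% dropout. Section 11.1 runs efficacy on both the FAS and the per-protocol set (PPS).

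**The concern.** Visit 4 is the only assessment after treatment stops, so it is the only visit that can show whether a cure lasted. If it is missed, the rule fills it with a result from Day 14 or Day 7, when the subject was on treatment or had just finished. A carried-forward cure cannot show re-infection, which section 5.2 counts as failure. The imputation rule thus removes the event that the follow-up visit is there to detect.

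Two things are at stake. Long-term cure is overstated in any arm where cured subjects relapse unseen. In a non-inferiority comparison, if more relapses are hidden in the test arm than in the control arm, a real deficit shrinks and a pass becomes easier. The documents also describe no further assessment for a subject who leaves after refusing drug, so the missing outcomes cannot be recovered later.

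**Working it through.** **Reproducing the planned size.** Section 3.2 gives 85% efficacy, one-sided α of 5%, 80% power and 158 per group. It states no margin. With equal true rates, n = (1.645 + 0.842)² × 2 × 0.85 × 0.15 / margin². A 10-point margin gives 6.183 × 0.255 / 0.01 = 157.7, so 158, an exact match. Margins of 9 and 11 points give 195 and 131. The 10-point margin is therefore an inference, though a close-fitting one. The total of 380 is 158 × 1.2 = 189.6, so 190 per arm (1:1 allocation assumed).

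**Model.** In each arm, with a fraction d missing visit 4, the recorded week-4 cure is (1 − d) × true week-4 cure + d × carried-forward cure. Missing subjects are taken to have the same true week-4 cure as those seen. The chance of a non-inferiority pass is Φ[(difference + 0.10)/SE − 1.645], with unpooled SE and 190 per arm.

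**Baseline.** True week-4 cure is assumed to be 85% (itraconazole) versus 75% (miconazole), exactly at the inferred margin. The correct false-pass rate is then Φ(−1.645) = 5%.

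**Main illustration.** Day 14 cure is 85% in both arms, so the whole gap is test-arm relapse, and d = 20% in each arm.
- Control: 0.8 × 0.85 + 0.2 × 0.85 = 0.85
- Test: 0.8 × 0.75 + 0.2 × 0.85 = 0.77, which overstates test-arm cure by 2 points
- Difference: −8.0 points
- SE = √(0.85 × 0.15/190 + 0.77 × 0.23/190) = 0.0400
- Pass rate: Φ(0.02/0.0400 − 1.645) = Φ(−1.145) ≈ 12.6%

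**Other assumed patterns, same true 10-point gap.**

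| Pattern (carried-forward cure, control vs test) | Missing, control / test | Gap shown | False-pass rate |
| --- | --- | --- | --- |
| Day 14, 85% vs 85% | 5% / 5% | 9.5 | 6.4% |
| Day 14, 85% vs 85% | 10% / 10% | 9.0 | 8.1% |
| Day 14, 85% vs 85% | 10% / 30% | 7.0 | 18.7% |
| Day 14, 90% vs 85% (half the gap is relapse) | 20% / 20% | 9.0 | 8.2% |
| Day 14, 95% vs 85% (equal relapse, in points) | 20% / 20% | 10.0 | 5.0% |
| Day 7, 60% vs 40% (early dropouts) | 20% / 20% | 12.0 | 1.8% |

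The last two rows show that the direction is not fixed. Equal relapse does no harm to the difference, and early dropouts who carry a wider Day 7 gap make the test conservative.

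**Counting every missing subject as not cured.** With 20% missing in each arm, the rates are 0.8 × 0.85 = 0.68 and 0.8 × 0.75 = 0.60. The gap is again 8.0 points, and the pass rate is 10.8%. With 10% versus 20% missing, the gap is 0.765 − 0.60 = 16.5 points and the pass rate is 0.1%. This rule alone is not a safeguard for non-inferiority either.

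**The case against.** The strongest objection concerns direction. A reader might infer that last observation carried forward always pulls the arms together. The documents do not support that: they give no relapse rates and no dropout by arm, and the table includes patterns with no bias and with bias against the test arm. That part of the objection stands, so only the possibility of bias can be claimed.

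Three further limits also stand:
- A reader might take section 6.2 to withdraw everyone who stops drug. Its wording reaches subjects already lost to follow-up through refusing drug or testing, and it says only that "the last detection result can be considered as final result", which is permissive.
- A reader might object to carrying a Day 7 cure to Day 14. Section 5.2 accepts cure at Day 7 or Day 14, so nothing is added there. The problem lies at visit 4.
- The 20% in section 3.2 has no timing. Placing all of it between Day 14 and visit 4 is an upper-end scenario. Subjects who leave uncured carry failure forward.

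It can also be said that the PPS gives a second view. It does not answer the point: it is restricted to subjects who complete treatment and the case report form, so it leaves out the missing outcomes without recovering them. Requiring one evaluation after medication is a common FAS definition, and its effect here has not been quantified. Finally, imputation details often belong in the SAP, which is not shown, but the carry-forward rule is stated in the Protocol itself.

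**Conclusion.** The concern holds in a limited form. As written, a subject cured on treatment who misses visit 4 counts as cured in the long term. Long-term cure is overstated whenever such subjects relapse. The comparison can be biased towards a non-inferiority pass if relapse is commoner in the test arm.

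In the main illustration the false-pass rate rises from 5% to about 12.6%. Across the assumed patterns shown under carry-forward it runs from 1.8% to 18.7%. These figures rest on an inferred 10-point margin, a 1:1 split, and assumed cure, relapse and missingness rates. They show what the rule permits and do not forecast this trial's result. The change should be made, because the rule works against part of the primary outcome and is cheap to replace.

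**What to change.** In section 11.1:
- Do not carry cure forward to visit 4. Impute missing week-4 cure by multiple imputation within arm, from baseline and earlier visits.
- Add a tipping-point analysis that varies the outcome of missing subjects separately by arm. Keep last observation carried forward, and counting missing as not cured, only as sensitivity analyses.
- Define the FAS as all randomised subjects, as randomised. This also removes the difference between section 11.1 (evaluated after medication) and section 11.2 (evaluated after randomisation).

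In section 5, name visit 4 as the time point for long-term cure, so that the imputation has a fixed target.

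In section 6.2, separate stopping study drug from leaving the study, and keep the scheduled visits 3 and 4 for subjects who stop drug but still consent. This concerns data collection only and does not touch when drug should be stopped.

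The cost is protocol wording and some analysis work, since the visits are already scheduled. The downside is a slightly lower reported long-term cure rate and a wider interval.

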3.2 Sample size

In the present data of studies on the efficacy of itroconazole treating oral candidiasis, an 85% efficacy rate was assumed. To achieve 80% power with a significance level of 10%(α level, 5%; βlevel, 20%; both 1-sided), 158 participants per group would be required. To compensate for a potential 20% dropout rate, a sample size of 380 participants in total will be applied for this study.

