6.1 Withdraw decided by researcher

Subject withdrew the study indicates that the enrolled subject cannot continue research at certain condition, and researcher decides the subject to withdraw from research process.

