11.2 Statistical analysis method

Analysis and reporting of the results will follow the CONSORT guidelines for reporting randomised controlled trials. All participants who had at least 1 efficacy evaluation after randomization will be included in the analysis. Safety analyses included all patients who received at least 1 dose of study medication. The trial data will be processed and analyzed by an independent statistician, who will be blinded to participant allocation.

A non-inferiority statistical approach was used. Continuous data were compared using either the Student t test or the Mann-Whitney nonparametric test. For binary data, the 2 treatment groups were compared using the chi-square test or the Fisher exact test. The Mantel-Haenszel test was used to evaluate ordinal quantitative data.

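### The per-protocol set in section 11.1 has no exception for outcome-related stopping, so it can drop documented failures and is a weak check on the FAS

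*Protocol*

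**What the plan says.** - **PPS (Protocol 11.1).** Members must meet the eligibility criteria. The rule then admits those "completing therapeutic scheme. Analysis (per protocol, PP) is taken on data of all cases consistent with research scheme, with good dependency and completion of filling" of the CRF, where dependency evidently means compliance. Nothing is said about patients who stop for lack of response or for an adverse event.
- **Sets used for efficacy (11.1).** "Baseline comparative analysis and curative effect analysis are conducted based on" the FAS and the PPS. Neither is ranked above the other.
- **FAS (11.1).** Randomised patients with at least one evaluation after medication, with missing later evaluations filled by last observation carried forward (LOCF). Section 6.2 treats the last result of a withdrawn patient as final and sends that patient to the full data set. Section 11.2 includes everyone with at least one efficacy evaluation after randomisation.
- **Type of comparison (11.2).** "A non-inferiority statistical approach was used".
- **Blinding and withdrawal.** Section 3.4 leaves participants, investigators and assessors unblinded. Under 6.1 the "researcher decides the subject to withdraw from research process", on grounds that are not specified. Sections 5.3 and 6 provide for withdrawal after serious adverse events.
- **Outcome timing.** Section 5.2 allows cure to be judged at Day 7 or Day 14 and counts improvement below 60% and persistence of Candida as failure. Section 8.3 schedules an efficacy evaluation after one week.

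**The concern.** Treatment lasts two weeks and efficacy is already assessed after one. Under 5.2 a patient can be a failure on the Day 7 assessment. If that patient then stops, 11.1 removes the patient from the PPS because the course was not completed. The reason for exclusion can therefore be the outcome itself. In an open-label trial with unspecified grounds for investigator withdrawal, it can also differ by arm.

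In a non-inferiority trial the PPS normally stands beside the FAS as a check that protocol deviations and imputation have not blurred a real difference. A PPS that selects on finishing treatment describes cure among patients who did well enough to finish. Agreement between FAS and PPS is then less reassuring than it looks, and disagreement is hard to interpret.

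**Working it through.** **1. The plan's own figure.** Section 3.2 states that "an 85% efficacy rate was assumed" and: "To achieve 80% power with a significance level of 10%(α level, 5%; βlevel, 20%; both 1-sided), 158 participants per group would be required". No margin is stated. Solving for it with equal rates of 85%, one-sided 5% and 80% power:

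margin = sqrt[2 × 0.85 × 0.15 × (1.645 + 0.842)² / 158] = 0.0999, about 10 points.

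Conversely, a 10-point margin gives n = 2 × 0.1275 × (1.645 + 0.842)² / 0.01 = 157.7, so 158 per group. The 10-point margin is an inference. The total of 380 reproduces as 158 × 1.2 ≈ 190 per arm.

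**2. What the PPS does to the cure rates.** Assumptions, none of them in the protocol: true cure is 85% on itraconazole and 75% on miconazole, a true deficit of 10 points. Everyone who leaves the PPS is a failure.

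*Case A: the same share f of failures stops in each arm.* PPS rate = p / [1 − (1 − p)f].

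| f | Itraconazole | Miconazole | PPS deficit |
|---|---|---|---|
| 0% | 85.0% | 75.0% | 10.0 points |
| 10% | 0.85/0.985 = 86.3% | 0.75/0.975 = 76.9% | 9.4 points |
| 25% | 0.85/0.9625 = 88.3% | 0.75/0.9375 = 80.0% | 8.3 points |
| 50% | 0.85/0.925 = 91.9% | 0.75/0.875 = 85.7% | 6.2 points |

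At f = 50% the early stoppers are 7.5% of the itraconazole arm and 12.5% of the miconazole arm, inside the 20% dropout allowance in 3.2.

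*Case B: early-stopping failures set as a share of all randomised patients.* PPS rate = p / (1 − share).

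| Miconazole share | Itraconazole share | Miconazole PPS rate | Itraconazole PPS rate | PPS deficit |
|---|---|---|---|---|
| 10% | 5% | 83.3% | 89.5% | 6.1 points |
| 5% | 5% | 78.9% | 89.5% | 10.5 points |
| 5% | 10% | 78.9% | 94.4% | 15.5 points |

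**3. Why the two cases differ.** Equal shares of randomised patients are not equal behaviour among failures. A 5% share is one third of the itraconazole failures (5/15) but one fifth of the miconazole failures (5/25). With 5% on itraconazole, the break-even miconazole share x solves 0.75/(1 − x) = 0.8947 − 0.10, so x = 5.6%. Above that the deficit shrinks; below it the deficit grows.

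**4. If the PPS alone decided.** Probability of declaring non-inferiority = Φ[(0.10 − PPS deficit)/SE − 1.645], with a 10-point margin and 190 randomised per arm less the early stoppers. In Case A it is 5.0%, 6.8%, 11.4% and 30.1% for f = 0%, 10%, 25% and 50%. In Case B it is 27.8% (10% vs 5%), 3.7% (5% vs 5%) and 0.1% (5% vs 10%).

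**The case against.** Four points can be made for the plan.

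- **The patients are not lost.** A reader might infer that they leave the efficacy analysis altogether. They do not. The FAS in 11.1 keeps anyone with one evaluation after medication, and 6.2 and 11.2 confirm it. This stands: the problem is confined to the PPS.
- **The direction is not fixed.** A reader might infer that a completer PPS always pushes a non-inferiority trial towards similarity. Case B shows that it need not, and the protocol gives no stopping rates by arm or reason. This stands too. Shrinkage is what follows if failing patients are equally likely to stop in either arm, but that is an assumption. Early stoppers who were already cured at Day 7 would also offset part of the effect.
- **The false-claim rates do not describe this trial.** They need a decision on the PPS alone and a margin that the protocol does not state. No section makes the PPS decisive. This stands.
- **The pairing is conventional, and details usually go to the SAP.** A completer PPS beside an FAS is common, and section 10 asks for CRF omissions to be corrected, so the CRF condition may exclude few patients. This lowers the priority. It does not remove the point, because 11.1 states the completion rule outright and gives no exception for stopping that is related to outcome.

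**Conclusion.** The point holds in a limited form. As written, 11.1 excludes patients from the PPS on a post-randomisation event that can be the treatment outcome, in a trial where those who can withdraw patients know the arm. This can bias the PPS comparison and weakens it as a check on the FAS. The FAS analysis is not affected by this rule.

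On assumed cure of 85% versus 75%, a 10-point deficit becomes 9.4 to 6.2 points in the PPS when 10% to 50% of failures stop in both arms. It becomes 10.5 to 15.5 points when the early-stopping shares of randomised patients are equal at 5%, or are 5% on miconazole against 10% on itraconazole. These figures rest on assumed stopping patterns and on every leaver being a failure. The documents do not support a claim that the trial's false-positive rate is inflated, or that the result must lean towards non-inferiority. This is a cheap improvement to the plan, not a flaw that invalidates it.

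**What to change.** Reword the PPS definition in 11.1:

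1. Define membership by eligibility and by major deviations unrelated to outcome, listed in advance.
2. Keep patients who stop, or are withdrawn, for lack of efficacy, and score them as failures.
3. Keep patients who stop for an adverse event after a post-baseline efficacy evaluation, and score them by their observed result: cured only if the definition in 5.2 was met, otherwise failure. Scoring all of them as not cured would conflict with the Day 7 cure definition in 5.2 and the last-result rule in 6.2, and could give one patient different outcomes in the FAS and the PPS.
4. Replace the CRF completion condition with a requirement for the cure assessment or a documented failure.
5. Have membership decided masked to arm by the blinded statistician named in 11.2.

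No new visits or measurements are needed. The reason for stopping must be on record for every such patient. Section 6.2 already requires this for voluntary withdrawal, and 6.1 should say the same for investigator withdrawal. The cost is slightly lower PPS cure rates and a PPS that no longer consists purely of full-course completers.
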